## Abstract

**Background:**

Age-related macular degeneration (AMD) is the leading cause of blindness among older adults in the developed world. The only treatments currently available, such as ranibizumab injections, are for neovascular AMD, which accounts for only 10 to 15% of people with the condition. Hypoxia has been implicated as one of the primary causes of AMD, and is most acute at night when the retina is most metabolically active. By increasing light levels at night, the metabolic requirements of the retina and hence the hypoxia will be considerably reduced. This trial seeks to determine whether wearing a light mask that emits a dim, green light during the night can prevent the progression of early AMD.

**Methods/design:**

ALight is a Phase I/IIa, multicentre, randomized controlled trial. Sixty participants (55 to 88 years old) with early AMD in one eye and neovascular AMD (nAMD) in the fellow eye will be recruited from nAMD clinics. They will be randomized (in the ratio 1:1), either to receive the intervention or to be in the untreated control group, stratified according to risk of disease progression. An additional 40 participants with healthy retinal appearance, or early AMD only, will be recruited for a baseline cross-sectional analysis. The intervention is an eye mask that emits a dim green light to illuminate the retina through closed eyelids at night. This is designed to reduce the metabolic activity of the retina, thereby reducing the potential risk of hypoxia. Participants will wear the mask every night for 12 months. Ophthalmologists carrying out monthly assessments will be masked to the treatment group, but participants will be aware of their treatment group. The primary outcome measure is the proportion of people who show disease progression during the trial period in the eye with early AMD. A co-primary outcome measure is the rate of retinal adaptation. As this is a trial of a CE-marked device for an off-label indication, a further main aim of this trial is to assess safety of the mask in the cohort of participants with AMD.

**Trial registration:**

International Standard Randomised Controlled Trials Register: ISRCTN82148651

## Background

Age-related macular degeneration (AMD) is the leading cause of blindness in the developed world [1] and is responsible for more than 50% of visual impairment registrations in the UK [2]. For the majority of people with AMD, there is no treatment. The remaining 10 to 15% of people with the advanced, neovascular, form of the disease (nAMD) are mainly treated with intra-ocular injections of ranibizumab, an anti-vascular endothelial growth factor agent [3]. Follow-up treatment for these patients is long-term and places a significant burden on the UK National Health Service. Indeed, advanced AMD currently costs the British economy £1.2 billion to £3.7 billion per annum [2,4,5]. Furthermore, the disease is associated with depression, falls and social isolation [6,7]. Given this significant socioeconomic problem, there is a great need to evaluate potential therapeutic interventions that attempt to treat the disease at an early stage, to prevent vision loss from occurring.

Age-related macular degeneration is characterized by the dysfunction and death of photoreceptors in the central retina. There is an increasing amount of evidence to suggest that hypoxia plays a major role in its pathogenesis [8,9]. This has been attributed to various factors, including a disruption of choroidal circulation [10-13], and thickening and deposition of drusen at Bruch’s membrane [9,14]. The latter increases the distance over which oxygen must travel to reach the retinal pigment epithelium from the choroidal circulation. Disease-related changes to Bruch’s membrane also impair the diffusion of nutrients and growth factors, which consequently exacerbates choroidal perfusion abnormalities, promoting further hypoxia [8,15].

Even in the healthy retina, intraretinal oxygen profiles obtained from animals show that the oxygen tension at the proximal side of the photoreceptor inner segments is close to zero in darkness [16,17]. This is attributable to the metabolic demand of the ‘dark current’ in the retina’s approximately 120 million rods [18]. When this limited supply of oxygen to the outer retina is further compromised by the changes to the choroidal circulation and Bruch’s membrane that occur in AMD, hypoxia may result. This hypoxia could be the precursor for increased vascular endothelial growth factor production and apoptosis [19,20].

The fragile balance between metabolic demand and oxygenation is exemplified functionally by the adverse effects of hypoxia on colour vision [21-23], dark adaptation [24,25], mesopic sensitivity [26] and the electroretinogram [12,27-29]. To date, there is no direct evidence of the effect of hypoxia on visual function in AMD. However, there is evidence that scotopic threshold elevation and prolonged electroretinogram implicit times are associated with areas of reduced choroidal blood flow in AMD [30,31] and pilot data from our laboratory show a transient reduction in scotopic thresholds in an individual with early AMD whilst inhaling oxygen.

Environmental manipulation of light levels can substantially reduce the metabolic demands on the outer retina, thereby reducing the need for oxygen, and potentially providing an intervention that would delay the progression of conditions with a hypoxic aetiology [32]. A pilot study by Arden et al. [33] found no adverse effects from the provision of low-level night lighting over the course of 12 months in individuals with diabetic retinopathy [33]. Furthermore, a recent clinical trial in patients with diabetic macular oedema who wore a low-level light mask during the night for 6 months reported a reduction in oedema and an improvement in functional measures, which was attributed to the obviation of night-time hypoxia [34]. In this trial, we will be using the same intervention (low-level light therapy) to determine its ability to prevent the development of AMD.

## Methods/design

### Trial objectives

The primary aim of this study is to collect preliminary Phase I/IIa proof-of-concept trial data from people with early AMD in one eye and advanced nAMD in the fellow eye, recruited from a hospital nAMD clinic, in order to assess the impact of low-level night-time light therapy, compared with no intervention, on disease progression in the eye with early AMD. A further main aim of this trial is to assess safety of the mask in the cohort of participants with AMD.

The secondary aims of the study are to:

1. Establish the effect of low-level night-time light therapy, compared with no-treatment control, on secondary outcome measures, including: change in drusen volume from baseline in the eye with early AMD; ranibizumab retreatment rates in the fellow eye with nAMD; progression of early AMD on the basis of change in functional outcome measures; change in health-related quality of life (assessed using the EuroQol EQ-5D instrument); change in self-reported visual function assessed using the 48-item Veterans Affairs Low-Vision Visual Functioning Questionnaire (VA LV VFQ-48).

2. Establish the acceptability of low-level night-time light therapy in people with AMD by monthly qualitative interviews.

3. Determine the effect of low-level night-time light therapy on sleep patterns by conducting the Pittsburgh Sleep Quality Index (PSQI) questionnaire every month with both intervention arms by interview with the study investigator.

4. Establish the relationship between baseline functional biomarker outcomes and the severity of AMD (assessed using the simplified Age-Related Eye Disease Scale (AREDS) and initial drusen volume).

5. Evaluate the ability of all clinical tests to act as prognostic biomarkers for AMD progression.

6. Evaluate the ability of all clinical tests to act as predictive biomarkers for low-level night-time light therapy in people with AMD.

7. Compare the sensitivity of all clinical tests to disease progression over 12 months.

### Study design and setting

ALight is a Phase I/IIa prospective proof-of-concept randomized controlled trial, consisting of two parallel groups. Trial recruitment and data collection will take place at the Medical Retina Clinic, Bristol Eye Hospital. Additional cross-sectional data will be collected from people with healthy eyes, or only early signs of AMD, at the Cardiff University School of Optometry and Vision Sciences.

### Eligibility criteria

#### **
*Inclusion criteria*
**

• Between the ages of 55 and 88 years.

• Early Treatment of Diabetic Retinopathy Study (ETDRS) visual acuity of 0.3 logMAR (Snellen 20/40 or 6/12) or better in the test eye.

• Early AMD in the study eye.

• nAMD in the fellow eye, within a month of the third Ranibizumab injection (trial only).

• Willing to adhere to allocated treatment for duration of trial.

#### **
*Exclusion criteria*
**

• Ocular pathology other than macular disease.

• Significant systemic disease or medication known to affect visual function.

• Systemic disease that would compromise participation in a 1-year study (trial only).

• Insufficient English language comprehension.

• Cognitive impairment as determined using an abridged Mini Mental State Examination [7].

• Oxygen mask worn at night.

#### **
*Suspension criteria for the trial*
**

• Participant wishes to discontinue the study.

• Serious adverse events (for example, conversion to nAMD in the test eye) or unexpected changes in clinical status.

### Interventions

Participants allocated to the treatment group will be given a 12-weekly disposable light mask (Polyphotonix Medical, UK) that presents organic light-emitting diode illumination (peak output 502 nm) to both eyes, to be used overnight for 12 weeks. Light masks will be replaced every 12 weeks at the participant’s routine appointment at the nAMD clinic so that the total duration of mask usage is 12 months.

The mask provides a luminance of 75 photopic cd/m^2^. When adjusted for the spectral sensitivity of rod photoreceptors, this equates to 186 scotopic cd/m^2^ [35]. Light transmission by the human eyelid has been found to range between 0.3% and 2% for light in the region of 500 to 505 nm [36-38]. Under these conditions, the pupil diameter in people in the age group 60 to 85 years is approximately 4 mm [39]. This will result in a retinal illuminance in the order of 23 scotopic Td (assuming an eyelid transmission of 1%).

The masks will be pre-programmed to function only between specific hours, that is, 8 pm to 8 am, to prevent misuse. Outside of these hours, they will not illuminate if worn. The mask is activated when a touch sensor on the device is gently covered with a finger for 3 seconds. It will deactivate if not worn continuously for the first 15 minutes, and after that, the light will remain on for the remainder of the 8-hour period.

Treatment acceptability will be evaluated during a monthly interview with the study investigator. Compliance data will be obtained at the monthly visit from the treatment group both (i) through evaluation of a diary of mask usage, and (ii) objectively through data collected on a chip in the mask itself (based on a sensor which logs when the mask is in contact with the face). This provides precise data on the hours the mask is worn each night by each participant. As each mask is programmed with the unique participant identification code, compliance data stored on-chip will be non-identifiable except via the password-protected electronic database.

The current management of patients with early AMD involves advising on lifestyle factors, such as stopping smoking and improving diet. The only other intervention that is based on evidence from a robust randomized controlled trial is the provision of a nutritional supplement consisting of high-dose antioxidants plus zinc. This AREDS group formula (vitamin C, 500 mg; vitamin E, 400 IU; beta carotene, 15 mg and zinc, 80 mg) has been shown to reduce risk of progression from early to advanced AMD by around 20% over 5 years in people with specific features of AMD [40]. However, a recent systematic review by the Cochrane Collaboration indicated that there may be an increased risk of mortality in individuals taking vitamin E and beta carotene supplementation [41]. As this is a recently published document, its advice is not reflected in the current guidelines for the management of AMD. For this reason, the low-level light therapy will be compared with a no-treatment control, rather than with the AREDS group formula as the best current intervention.

Participants in both groups will receive routine ophthalmological care for the eye with nAMD (that is, ranibizumab injections). If the eye with early AMD converts to nAMD, the participant will proceed to ranibizumab treatment for this eye also, and will be withdrawn from the study.

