### Outcome measures

This study includes two co-primary outcome measures, reflecting structural status and functional status.

1. The proportion of people who show ‘disease progression’ in the eye with early AMD during the 12 months of the study based on an increase in drusen volume beyond test-retest repeatability limits or a progression to advanced AMD. Software available for the Cirrus optical coherence tomography (OCT) system allows automated assessment of drusen volume. Irrespective of initial drusen volume, approximately 50% of people with AMD show a significant increase in drusen volume over the 12-month study period, that is, beyond test-retest 95% confidence intervals [42]. Conversion to advanced disease will also be considered to be an indicator of disease progression in this analysis. Data from a trial on a similar group indicates that about 10% of people meeting our inclusion criteria will develop advanced AMD within 12 months [43]. Hence, 60% of participants might be expected to show progression based on increased drusen volume or progression to late AMD. The development of advanced AMD will be determined on the basis of ophthalmologist diagnosis at the monthly follow-up appointments at the nAMD clinic.

2. The rate of retinal adaptation (time taken for photoreceptors to recover their sensitivity after being exposed to a bright adapting light).

Secondary outcome measures include: the change in drusen volume over the 12 month follow-up period; the number of ranibizumab retreatments required during the year in the fellow eye with nAMD (assessed through review of medical records at the end of 12 months); changes in visual function including chromatic thresholds, visual acuity and psychophysical 14 Hz flicker thresholds; self-report outcome measures, including health-related quality of life (EQ-5D) and visual function (VFQ-48) [44]; a sleep quality questionnaire (PSQI) and a semistructured interview (conducted monthly by interview) to determine intervention acceptability.

To obtain detailed information about the time course of any therapeutic action, the primary and the first of the secondary outcome measures (based on drusen volume) will be assessed at baseline and then at monthly intervals (using OCT images obtained at the regular nAMD clinic follow-up appointments).

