The ETDRS visual acuity will be assessed in each eye. Chromatic thresholds will be measured for the eye with early AMD using the Colour Assessment and Diagnosis test [48] (City Occupational Ltd). Contrast thresholds to a 14 Hz flickering stimulus will be measured for the eye with early AMD using the procedure outlined by Dimitrov et al. [49]. The rate of parafoveal cone dark adaptation will be determined for the eye with early AMD using a psychophysical procedure described previously [50]. Thresholds will be determined using a psychophysical method, based on a ‘3 down, 1 up’ staircase paradigm [50]. An array of white light-emitting diodes behind a diffusing filter will be used to light-adapt photoreceptors in the central 43.6° of the test eye (the output of the white light-emitting diodes will be modified by a Lee filter, HT015, to provide a retinal illuminance of 5.20 log phot Td.s^-1^, providing a bleach of 85% cone photopigment and 74% rhodopsin). All light levels fall within the safety guidelines set out in British Standard BS EN 15004-2 (2007) [51]. There will be an initial training phase, of around 5 minutes, then the adapting light will be presented, and finally recovery of visual thresholds will be monitored for 25 minutes after exposure to the adapting light.

Those individuals who are assigned to the treatment group will then be given a light mask, and provided with written and oral instructions on its use. There will also be a reprise of the key information provided in the participant information letter about follow-up appointments. Participants will be given written copies to take home of the PSQI questionnaire that will be used in the monthly interview.

#### **
*Monthly assessment*
**

The investigator will access the OCT images and medical records of all participants after they have attended the ranibizumab clinic for each monthly follow-up appointment. This will allow measurement of drusen volume on a monthly basis, which will allow the final analysis to include an assessment of the time course of any therapeutic action. Additionally, reviewing medical records will facilitate monitoring of the conversion rate to advanced AMD in the control and intervention groups in the eye with early AMD at baseline, and of ranibizumab retreatment rates in the eye with nAMD, for adverse event reporting purposes.

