Participants in both intervention groups will attend a short, monthly follow-up appointment following their routine ranibizumab clinic appointment, during which both groups will complete the PSQI sleep quality questionnaire. In addition, the treatment group will bring their mask along to each monthly visit to allow objective compliance data (nightly hours of use) to be exported from the device, retraining in mask use if required, functionality of the mask to be checked, masks to be replaced every 12 weeks, and a semistructured interview to be carried out to determine the acceptability of the intervention. These data will be used to address secondary objectives 2 and 3.

#### **
*Final (12-month) visit*
**

This visit will be the same as the baseline visit with the addition of a final semistructured interview assessing the acceptability of the intervention, and the questionnaires (PSQI, VA LV VFQ-48, Euroqol).

#### **
*Baseline cross-sectional study*
**

The 40 participants recruited only to the cross-sectional part of the study will undergo the tests outlined in the baseline assessment visit of the trial.

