### Statistical methods

It should be noted that, as a Phase I/IIa proof-of-concept study, this research is designed to assess the acceptability of this therapy for the participants, and to provide preliminary data to support a larger Phase III randomized controlled trial in the future, and so is not powered to detect small effect sizes. To maximize retention, all follow-up visits will be timed to coincide with scheduled appointments at the nAMD clinic. We will aim to recruit 60 people, which, allowing for 15% dropout through the year, should leave a final cohort of 51. This will be sufficient to detect a 50% reduction in people showing progression at a probability level of 0.2, with a power of 80%, and a change in the time constant of cone adaptation of 1 minute to be detected at a probability level of 0.05, with a power of 80%. The additional 40 participants enrolled into the cross-sectional part of the study will allow a total cohort of *n* = 100 to address secondary aim 4.

Analysis will be carried out on an intention-to-treat basis. There will be no interim analysis, but conversions to nAMD in the eye with early AMD at baseline, and ranibizumab retreatments for the fellow eye, will be recorded at each participant visit to the nAMD clinic for safety monitoring purposes.

This trial will primarily be concerned with providing information about the safety of the device in the treatment of AMD, and the magnitude of any treatment effect. On this basis, descriptive statistics will be carried out to summarize the demographic characteristics of the two groups, as well as the proportion of individuals showing disease progression in each group, the magnitude of changes in secondary outcome measures, including drusen volume, measures of visual function, and the self-report tests, and the fellow eye retreatment rates.

The primary outcome measure will be the proportion of patients demonstrating disease progression at 12 months. Comparisons will be performed using stratified Mantel-Haenszel tests and presented as forest plots.

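### Withdrawing participants whose study eye converts to nAMD leaves the adaptation co-primary measured in non-converters only, and 51 cannot be the evaluable number for both co-primaries

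*Protocol article*

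**What the plan says.** Two places in the protocol article end participation on conversion. Interventions states that "the participant will proceed to ranibizumab treatment for this eye also, and will be withdrawn from the study". The suspension criteria for the trial, under Eligibility criteria, list "Serious adverse events (for example, conversion to nAMD in the test eye) or unexpected changes in clinical status".

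Outcome measures makes the same event part of the first co-primary: "Conversion to advanced disease will also be considered to be an indicator of disease progression in this analysis". The second co-primary is the rate of retinal adaptation. Data collection methods says where and when it is measured. At baseline, "The rate of parafoveal cone dark adaptation will be determined for the eye with early AMD", which is the eye that may convert. For the final visit, "This visit will be the same as the baseline visit with the addition of a final semistructured interview" and the questionnaires. The monthly visits have OCT images, records review and the sleep questionnaire, but no functional tests. No exit test is described.

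Participant timeline has final outcome data collected from both groups at 12 months. Statistical methods says "Analysis will be carried out on an intention-to-treat basis" and sizes both co-primaries on one number: 60 recruited, "allowing for 15% dropout through the year, should leave a final cohort of 51".

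**The concern.** For a converter these statements cannot all hold. A person withdrawn from the study does not attend the 12-month visit, so cannot supply the final outcome data that Participant timeline expects or the adaptation value that an intention-to-treat comparison needs.

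The loss is not random. It is triggered by disease progression, which the mask is meant to change and which Safety monitoring accepts it might worsen. The 12-month functional comparison would therefore be made in a group defined after randomisation, and the two arms could be depleted differently. The regression planned for the seventh secondary aim, which relates functional change to drusen change, would also lose eyes that reached advanced disease.

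The sample-size paragraph has a related problem. A converter has a known progression outcome but no adaptation outcome, so the two co-primaries cannot have the same evaluable number.

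**Working it through.** **Who has what, under the rules as written**

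| Outcome | Converter's data |
|---|---|
| Progression (co-primary) | Known: counted as progressed |
| Adaptation rate (co-primary) | Baseline only |
| Drusen volume | Monthly values up to conversion; final value missing |
| Acuity, flicker and chromatic thresholds | No 12-month study value |
| VFQ-48, EQ-5D | Baseline (screening) value only |

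**Inputs**
- 60 recruited, 15% dropout, 1-minute change in the time constant, probability level 0.05, power 80% (Statistical methods). No SD and no sidedness are given; two-sided is assumed.
- About 10% develop advanced AMD in 12 months (Outcome measures).
- 1-year nAMD incidence 12.2%, interval 1.7% to 30.6% (Safety monitoring). This is the closer match to the rule, because only nAMD triggers withdrawal.

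**The plan's own figures**
- Cohort: 60 × 0.85 = 51, so 9 dropouts. Reproduced.
- Progression, 60% v 30%, level 0.2 two-sided, 25.5 per arm: power 0.82. Consistent with the stated 80%.
- Adaptation: not reproducible without an SD. Solving for the SD that gives 80%: SD = 1 / [(1.960 + 0.842) × √(2/25.5)] = 1.27 min. The noncentral t version gives 1.25 min.

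**Expected converters:** 60 × 0.10 = 6; 60 × 0.122 = 7.3.

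**Reading A: converters are additional to the 15%**

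The lower n subtracts both losses from 60; the higher applies the conversion rate to the 51. Power = Φ(1 / [SD × √(2/n per arm)] − 1.960), with SD 1.27.

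| Conversion | n for adaptation | Power |
|---|---|---|
| 1.7% | 50 | 79% |
| 10% | 60 − 9 − 6 = 45, or 51 × 0.90 = 45.9 | 75–76% |
| 12.2% | 60 − 9 − 7.3 = 43.7, or 51 × 0.878 = 44.8 | 74–75% |
| 30.6% | 33–35 | 61–65% |

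The noncentral t version gives 0.756, 0.747 and 0.737 at n = 46, 45 and 44. Progression keeps 51.

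**Reading B: converters are inside the 15%**
- Adaptation: 51 evaluable, power 80%.
- Progression: 51 + 6 = 57 at 10% conversion, because converters' outcome is known.
- Places left for all other dropout: 9 − 6 = 3, or 9 − 7.3 = 1.7, so 2 to 3 of 60 over a year.

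Under neither reading is 51 the evaluable number for both co-primaries.

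**The case against.** The strongest reply concerns power. A reader might infer that the stated 80% for adaptation is simply not delivered. The document does not support that. Someone withdrawn from the study can naturally be counted in a general dropout allowance, and on that reading the 80% stands. On the other reading the loss at the expected rates is 4 to 6 points, it rests on an SD derived from the very power in question, and the trial describes itself as proof-of-concept and not powered for small effects. All of this stands. What remains is that the protocol does not say which reading applies.

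A reader might also infer that the trial could miss harm altogether. It would not: conversion is counted in the progression co-primary and tracked in safety monitoring against a numerical monthly limit. The risk is confined to the functional and self-report comparisons.

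Next, missing-outcome methods are usually left to an analysis plan, and an article condenses the full protocol. That is fair for the choice of method. It does not answer an explicit rule that stops data collection, because an analysis plan cannot recover values that were never measured.

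Finally, a test after conversion would measure an eye under treatment for nAMD, so including that value is a choice of estimand. This stands, and is a reason to state the choice and add a sensitivity analysis. It is not a reason to make the choice by default through withdrawal.

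**Conclusion.** The concern holds for the 12-month functional and self-report outcomes. As written, the withdrawal rule restricts the adaptation co-primary to non-converters, which conflicts with the intention-to-treat statement. That conclusion needs no assumed rate or SD. It assumes only that withdrawal means what it says and that no exit testing exists; the article describes none.

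It does not hold for the progression co-primary. Nor is the stated power for adaptation shown to be wrong: the shortfall is conditional on converters being additional to the 15%, and its size depends on a two-sided test and the back-solved SD of about 1.25 min. The firm sample-size point is narrower: the two co-primaries have different evaluable numbers, and the protocol gives one.

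**What to change.** Reconcile the suspension criteria, Interventions, Outcome measures, Participant timeline and Statistical methods so that reaching the progression endpoint is separated from leaving data collection. This concerns follow-up only; no view is taken on mask use or treatment after conversion.

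- Keep converters in follow-up, with the 12-month functional tests and questionnaires wherever they can be done.
- Analyse them as randomised, and state how they enter the adaptation comparison. Add a sensitivity analysis for converters who cannot be tested; assigning them the worst rank is one option.
- State whether the 15% dropout includes converters, and give the evaluable number for each co-primary separately. If converters are additional and cannot be tested, restate adaptation at about 44 to 46 people and 74 to 76% power, with the SD used.

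The cost is protocol wording plus test time for about 6 to 7 people. The adaptation test takes about 30 minutes (around 5 of training and 25 of recovery). Because the protocol sends converters on to ranibizumab treatment, they can be expected to keep attending the clinic where study visits already take place. The change is best made before recruitment, since functional data not collected at 12 months cannot be recovered.
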